##### Novel biomarker development

We re-analyzed expression data from a large transcriptomic study (n = 491); there are significant gains in sensitivity when increasing from 10 to 30 samples within groups, and only a moderate benefit of increasing from 30 to 40 in each group [49]. Specificity requires fewer samples, as it stops improving significantly after 20 samples per condition. Thus, these results justify our sample size of 30 per study arm.

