##### Immunologic analyses

In our preliminary work, we used a bootstrap approach to estimate the expected estimation error for the AUC, sensitivity, and specificity for our T cell markers at our proposed training sample size (n = 30). We expected to be able to estimate the AUC within 0.10, the sensitivity within 0.17, and the specificity within 0.13 using single markers alone. We fully expect that combination biomarkers will lead to more accurate estimates (the combination marker accuracy cannot be estimated because our preliminary data lead to perfect predictions). However, the single marker predictions demonstrate that our sample size is large enough to estimate these quantities with sufficient accuracy.

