### Statistical analyses

#### Mtb killing, cytokine analyses, and cellular immune responses

For the Mtb killing (intracellular bacterial growth) assays, we will log-transform relative luminescence units and compare groups using ANOVA including nutrition status, parasite status, gender and any other significant covariate using a forward selection approach. For all analyses, if needed (e.g. skewed or bimodal data), we will apply a non-parametric Kruskal–Wallis test. For colony forming unit measurements, we will use a Poisson regression model that includes covariates using a forward selection approach. For cytokine analyses, markers will be compared using ANOVA or Kruskal–Wallis test. If needed, to correct for multiple comparisons, we will apply a Bonferroni adjustment. To understand the effect of parasite treatment and nutritional supplementation over time, we will use time-course repeated measurements on the same individual and a mixed linear model.

The predictive value will be evaluated by receiver operating characteristics (ROC) curve analysis and logistic regression modeling using covariate metadata. Because our preliminary data demonstrate a strong signal from these markers, we will split our cohort into a training set (n = 20 in each group) and a test set (n = 10 in each group) for cross-validation purposes. The markers will be evaluated for their predictive abilities individually, as well as in combination. The combination logistic regression biomarker will be selected using a forward-step approach, adding markers one at a time and evaluating the predictive value (cross-validation within the training set).

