#### RNA sequencing

RNA will be extracted from our samples and sequencing libraries will be prepared and sequenced on an Illumina sequencer as described in our previous work [50, 51]. We will perform transcriptomic analysis to understand mechanisms of immune modulation by undernutrition and parasitic infections. Data will undergo quality control, aligned to the most recent human reference genome (hg38) using RSubread, and feature counts will be estimated for each gene as in our previous work [50, 51]. We will use the edgeR package to determine differential gene expression based on a false discovery rate cutoff of 0.05. The data will be subjected to the following: (i) Transcriptional modular/network analysis; (ii) GSVA and ssGSEA scoring of multiple existing TB-related gene expression pathways using our TBSignature profiler (https://github.com/compbiomed/TBSignatureProfiler); and (iii) Ingenuity pathway analysis [51]. We will use the differentially expressed gene sets and/or existing biomarker genes to derive a logistic regression model to develop biomarkers of Mtb infection in undernourished HHC and see if these predict TB risk. To address response to nutritional supplementation and parasite treatment, we will apply a mixed model using the dream R package [52] to account for the repeated measures analysis. We will use an FDR threshold of 0.05 to control for multiple comparisons.

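### The immunologic sample size rests on marker precision at a training size of 30, but the plan trains on 20 and tests on 10 per group

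*Protocol article*

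**What the plan says.** In the protocol article, *Immunologic analyses* (under the sample size calculations) reports bootstrap estimation errors "for our T cell markers at our proposed training sample size", which it gives as n = 30. The figures are "We expected to be able to estimate the AUC within 0.10, the sensitivity within 0.17" and "the specificity within 0.13 using single markers alone". For combinations of markers it gives no figure, "because our preliminary data lead to perfect predictions", though it expects them to do better. From the single-marker figures it concludes that the sample is large enough.

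The analysis section, *Mtb killing, cytokine analyses, and cellular immune responses*, states "we will split our cohort into a training set" with 20 per group and a test set with 10 per group. Markers are to be assessed singly and in combination. The combination logistic model is built by forward steps, each judged by cross-validation inside the training set.

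Each arm has 30 participants (*Longitudinal follow-up*; *Novel biomarker development*), so training on 30 per group would leave nobody to test on.

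**The concern.** The argument for adequacy and the planned analysis use different sample sizes. Precision is quoted for 30, a size at which, on the per-group reading, nothing is trained or tested. No precision is quoted for the sizes that are used. The conclusion that the sample suffices, which the Discussion repeats in general terms for the immunologic results, is therefore not supported for the marker evaluation as planned.

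The test set matters most. It is the only part of the design that gives an accuracy estimate untouched by marker selection, and it is the smallest. A reader who relies on the sample size section would expect an AUC known to about 0.10 and would receive one considerably less certain.

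**Working it through.** **Inputs from the article.** Errors of 0.10 (AUC), 0.17 (sensitivity) and 0.13 (specificity) at n = 30; training set 20 per group; test set 10 per group; 30 per arm.

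**Assumptions.** The article does not define its error bound, and I take it as a 95% half-width. I take n = 30 as per group, since *Novel biomarker development* speaks of 30 per study arm. Errors are taken to scale with 1/√n at the same operating point.

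**1. Are the stated figures coherent?** The bootstrap cannot be rerun without the preliminary data, so this is a plausibility check.
- Proportions: half-width = 1.96·√(p(1−p)/30). A value of 0.17 implies p of about 0.66, and 0.13 implies p of about 0.84.
- AUC (Hanley-McNeil): SE² = [A(1−A) + (n−1)(u−A²) + (n−1)(v−A²)]/n², with u = A/(2−A) and v = 2A²/(1+A). A half-width of 0.10 at 30/30 implies A of about 0.85.
- They cannot be standard errors at 30 per group, because the largest possible value for a proportion is √(0.25/30) = 0.091.

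The figures are thus coherent as 95% half-widths at 30 per group. This does not prove the per-group reading, because at 15 per group they are also attainable (sensitivity 0.87, specificity 0.93, AUC 0.93).

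**2. Scaling to the planned sizes.** Multiply by √(30/n), which is √1.5 = 1.22 at 20 and √3 = 1.73 at 10.

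| Per group | AUC | Sensitivity | Specificity |
|---|---|---|---|
| 30 (stated) | 0.10 | 0.17 | 0.13 |
| 20 (training) | 0.12 | 0.21 | 0.16 |
| 10 (test) | 0.17 | 0.29 | 0.23 |

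Hanley-McNeil half-widths at an assumed AUC of 0.85 agree: 0.099 at 30/30, 0.122 at 20/20 and 0.176 at 10/10. For assumed AUCs of 0.80, 0.85 and 0.90, the 10/10 half-width is 0.20, 0.18 and 0.15. A held-out AUC of 0.85 would be compatible with values from about 0.67 (0.85 − 0.176) up to 1.

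**3. If n = 30 were a total (15/15).** At 20 per group the factor is √(15/20) = 0.87, giving 0.09, 0.15 and 0.11, so training would meet the stated figures. At 10 per group the factor is √(15/10) = 1.22, giving 0.12, 0.21 and 0.16, so the test set would still miss them.

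**4. Bias or imprecision?** Forward selection by 5-fold cross-validation was simulated with training 20/20 and test 10/10. The 15 candidate markers are an assumption, since the article gives no number. There were 200 replicates per setting.

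| Setting | Cross-validated training AUC | Held-out AUC | True AUC of chosen model |
|---|---|---|---|
| 15 noise markers | 0.74 | 0.50 | 0.50 |
| Two real markers, 0.8 SD each | 0.84 | 0.69 | 0.69 |

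The held-out estimate centres on the truth, with a standard deviation of about 0.13 around it. The training figure is too high.

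**The case against.** The trial is described as exploratory, and the Discussion concedes the small arms. The quoted errors are for single markers only, and the article openly declines to give one for combinations, so it never promised a test-set precision in so many words. It also does not say that n = 30 is per group. All of this stands, and it limits the weight of the point. It does not remove the mismatch: the adequacy of the sample is inferred from those errors, and the test set falls short on either reading of n. A prespecified single marker assessed on all 30 per group would have the stated precision, but the plan describes a split and does not say that this is what it will report.

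Stronger readings are tempting, and the article does not support them:

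- **That the selection steps make the reported accuracy optimistic.** Selection is confined to the training set and a test set is held out. Optimism attaches to the training figure only.
- **That the RNA classifier leaks.** *RNA sequencing* says "We will use the differentially expressed gene sets and/or existing biomarker genes to derive a logistic regression model". It states neither selection on the full data nor a 20/10 split, and a condensed article may leave that detail to the full plan. A null simulation that forces in the top 10 of 10,000 noise genes, chosen on all the data, does give a test AUC of 0.97 to 0.98. The article's rule is a false discovery rate of 0.05, however. With t-tests and Benjamini-Hochberg as a stand-in, any gene passed in only 5% of 500 null datasets, and never more than two.
- **That training on 20 contradicts the article's own case for 30.** The statement that "there are significant gains in sensitivity when increasing from 10 to 30 samples within groups" concerns transcriptomic data, not the T cell markers that are split. The same section says specificity needs fewer samples and gains little beyond 20.
- **That perfect preliminary prediction makes the logistic model unusable.** Separation makes coefficients diverge but does not prevent ROC evaluation, which is the planned measure. Penalised regression would be a reasonable preference; it does not correct an error.

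**Conclusion.** The point holds as an inconsistency about sample size and precision. *Immunologic analyses* and the analysis section give different training sizes, and the precision used to justify the sample does not apply to the split that is planned. On the per-group reading, errors are about 22% larger than stated in training and about 73% larger in the test set. If 30 is a total, only the test set falls short, by about 22%. These sizes rest on root-n scaling and an unchanged operating point; the coherence check and the AUC half-widths also take the stated errors as 95% half-widths.

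The consequence is an imprecise held-out estimate, not a biased one, provided the test set takes no part in selection. The group comparisons and the mixed models are unaffected.

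**What to change.** Reconcile the training size in the two sections and say whether n = 30 is per group or a total. Then choose one of two routes:

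1. **Keep the split.** State the expected precision for 20 per group (training) and 10 per group (test), preferably by rerunning the bootstrap at those sizes. Soften the statement that the sample is large enough for sufficient accuracy. Confirm that the test set takes no part in selection, since the article loosely labels its purpose as cross-validation. The cost is wording and a less favourable stated precision.
2. **Drop the single split.** Use repeated nested stratified cross-validation on all 30 per arm, with every marker-selection step repeated inside the folds. Each participant then contributes out-of-fold predictions, so the estimate draws on 30 per group instead of 10; repeating the folds adds no participants. The cost is some computing time and a slightly longer explanation.

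In either case, state which accuracy estimate will be reported as the result. The cross-validated training figure from forward selection should not be that estimate. Neither route needs more participants or samples.

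### The combination immune biomarker relies on forward-step logistic regression with no named penalty, although preliminary data predicted perfectly: if that signal recurs, selection hits a ceiling and the fit can separate

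*Protocol article*

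**What the plan says.** In the sample size section on immunologic analyses, the Protocol article gives expected precision for single T-cell markers: "estimate the AUC within 0.10, the sensitivity within 0.17, and the specificity within 0.13 using single markers alone". For combinations it gives none: "the combination marker accuracy cannot be estimated because our preliminary data lead to perfect predictions".

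The statistical section on Mtb killing, cytokine analyses and cellular immune responses fixes the data split: "we will split our cohort into a training set (n = 20 in each group) and a test set (n = 10 in each group". It fixes how the combination is built: "The combination logistic regression biomarker will be selected using a forward-step approach, adding markers one at a time". It also fixes what each step is judged on: "evaluating the predictive value (cross-validation within the training set". Performance is described in general terms: "The predictive value will be evaluated by receiver operating characteristics (ROC) curve analysis and logistic regression modeling using covariate metadata".

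The RNA sequencing section plans a second model of the same family, to "derive a logistic regression model to develop biomarkers of Mtb infection in undernourished HHC and see if these predict TB risk".

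Neither section names an estimator, a penalty, the numerical selection criterion or a provision for separation.

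**The concern.** Perfect prediction by a linear combination of markers is complete separation. A logistic likelihood then has no maximum. Coefficients grow until the software stops, fitted probabilities go to 0 or 1, and Wald intervals mean nothing. The article reports perfect prediction and then chooses a model family and a stepwise rule that are vulnerable to exactly that, without a safeguard.

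The selection rule has its own weakness. With strong markers and 20 per group, cross-validated AUC soon reaches its upper limit and cannot rank what remains. Which markers enter, and how many, is then partly arbitrary. At stake are the composition of the panel, its published weights, and any predicted risk or adjusted estimate taken from it.

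**Working it through.** **1. The plan's own precision figures.** They come from a bootstrap of data that are not shown, so they cannot be reproduced directly. As a plausibility check, assume 30 per group and 95% half-widths.

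- AUC (Hanley–McNeil): SE² = [A(1−A) + (n−1)(a−A²) + (n−1)(b−A²)]/n², with a = A/(2−A) and b = 2A²/(1+A). At A = 0.84, n = 30: a = 0.724, b = 0.767, SE = 0.052, half-width 1.96 × 0.052 = 0.102. At A = 0.86 it is 0.096.
- Proportions: 1.96√(p(1−p)/30) is 0.170 at p = 0.66 and 0.131 at p = 0.84.

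The stated 0.10, 0.17 and 0.13 are therefore consistent with a single-marker AUC near 0.85. That value is inferred, not stated.

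The precision statement is made "at our proposed training sample size (n = 30", whereas the analysis section trains on 20 per group.

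**2. How often a fixed marker set separates.** Assumptions: two groups and independent normal markers with group shift √2·z(AUC). Separation was tested by linear programming, 400 runs per cell.

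| Per group | Single AUC | 2 markers | 3 | 4 | 6 |
|---|---|---|---|---|---|
| 20 | 0.80 | 0% | 3% | 15% | 69% |
| 20 | 0.85 | 1% | 14% | 50% | 93% |
| 20 | 0.90 | 9% | 50% | 84% | 100% |
| 30 | 0.85 | 0% | 2% | 20% | 84% |
| 30 | 0.90 | 1% | 24% | 67% | 98% |

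**3. The stated selection rule.** The table forces markers in; the plan adds them on cross-validated predictive value. That was simulated with 20 + 20, 10 candidate markers, mean AUC over five folds as the criterion, stopping at no gain, 150 runs per cell. The number of candidates, the folds and AUC as criterion are assumptions.

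| Correlation | Single AUC | Final model separated | Criterion reached 1.0 | Best candidates tied at some step |
|---|---|---|---|---|
| 0.3 | 0.85 | 10% | 28% | 55% |
| 0.3 | 0.90 | 20% | 65% | 57% |
| 0 | 0.85 | 53% | 93% | 68% |
| 0 | 0.90 | 46% | 98% | 75% |

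A second simulation of the same rule gave about 12–53% separated and 28–98% at the ceiling.

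The ties are easy to explain. Five folds of 20 + 20 leave 4 + 4 held out, which is 16 pairs per fold. The mean AUC over five folds can only move in steps of 1/80 = 0.0125.

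**4. What separation does to the fit.** In separated 20 + 20 training sets (2–4 markers, single AUC 0.85–0.90, true coefficients 1.5–1.8), 150 runs per setting, each evaluated on 2,000 new subjects; ranges are of medians across settings:

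| | Unpenalised, 25 iterations | Firth |
|---|---|---|
| Largest coefficient | 26–32 | 2.1–3.4 |
| Calibration slope | 0.06–0.09 | 0.61–1.00 |
| Brier score | 0.075–0.117 | 0.055–0.090 |
| AUC | 0.955–0.980 | 0.956–0.981 |
| Accuracy at 0.5 | 0.878–0.922 | 0.882–0.926 |

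Replacing the 25-iteration stop by a ridge of 10⁻⁶ moves the largest coefficient to 38–70, so the weights reflect the stopping rule. Ranking is almost untouched: AUC differs by at most about 0.002.

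**5. What the selection rule costs.** In the second simulation of step 3, ridge on all candidates with a cross-validated penalty was compared with the forward-step model. Out-of-sample AUC rose by about 0.05–0.08 and accuracy by about 6–12 percentage points, and the Brier score fell. This loss comes from stopping early on a saturated criterion, not from separation itself.

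**The case against.** Four objections deserve an answer.

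- **The estimator is not stated.** A reader might infer ordinary maximum likelihood, but the article names only a model family and a selection strategy. Ridge, elastic-net and Firth fits are all logistic regression, and an analysis plan that is not shown could name one. This stands, and is why the separation argument is conditional on an unpenalised fit. It does not cover the selection rule, which the article fixes itself.
- **Perfect prediction may not recur.** It was seen in preliminary data whose size, contrast and combination method are not given, and the article does not say it expects the same in the trial. This also stands. With single-marker AUC 0.75, even forced entry by likelihood up to four markers (correlation 0.3) separated at most 3% of training sets.
- **The planned measures are ROC-based.** No calibration measure or use of predicted risk is stated for this score, and for a fixed marker set AUC is essentially unaffected. This stands for the fit. It does not stand for marker choice, where AUC and accuracy are lost as well.
- **A plateau in cross-validated performance is a natural place to stop.** That is fair when the plateau reflects true performance. With 16 pairs per held-out fold, a value of 1.0 mostly reflects the coarseness of the criterion.

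A reader might also infer that no confidence interval could be reported. That goes too far: intervals for AUC, sensitivity and specificity remain available, and the article promises no odds ratio for the combination score.

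**Conclusion.** The point holds in conditional form. If the strong preliminary signal recurs, forward selection on a bounded criterion with 20 per group will often saturate (28–98% of simulated runs), and in about 12–53% of training sets the final model will be completely separated. Under separation an unpenalised fit has no finite coefficients, and its weights, Wald intervals and predicted probabilities are artefacts of the software.

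These shares assume a two-group contrast, ten candidate markers, five-fold AUC and single-marker AUCs of 0.85–0.90. They fall with weaker or correlated markers and larger groups, and the lower end is soft because it depends on fold assignment and the stopping rule. The gain from ridge depends on how many candidates carry signal, which the article does not give.

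The documents do not support saying that the score has no finite coefficients as a matter of course. For the RNA model the same reasoning applies, since genes can outnumber participants, but no calculation was made. This is a cheap improvement worth making in a trial that calls itself exploratory; it does not undermine the ROC results.

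**What to change.** - **Combination immune biomarker:** replace forward-step selection with ridge or elastic-net logistic regression on the candidate markers. Choose the penalty inside the training set by cross-validated log-loss or Brier score, which still distinguish models after AUC has reached 1.0. If only a few markers, chosen beforehand, are kept, use Firth logistic regression instead.
- **RNA sequencing biomarker:** name the same kind of penalised fit.

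The cost is wording in the analysis plan and standard software, with no new data or participants. Coefficients will be shrunken and cannot be read as unbiased odds ratios. Ridge gives a less sparse panel; elastic-net keeps it sparse if a short list is wanted.

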#### RNA sequencing

RNA will be extracted from our samples and sequencing libraries will be prepared and sequenced on an Illumina sequencer as described in our previous work [50, 51]. We will perform transcriptomic analysis to understand mechanisms of immune modulation by undernutrition and parasitic infections. Data will undergo quality control, aligned to the most recent human reference genome (hg38) using RSubread, and feature counts will be estimated for each gene as in our previous work [50, 51]. We will use the edgeR package to determine differential gene expression based on a false discovery rate cutoff of 0.05. The data will be subjected to the following: (i) Transcriptional modular/network analysis; (ii) GSVA and ssGSEA scoring of multiple existing TB-related gene expression pathways using our TBSignature profiler (https://github.com/compbiomed/TBSignatureProfiler); and (iii) Ingenuity pathway analysis [51]. We will use the differentially expressed gene sets and/or existing biomarker genes to derive a logistic regression model to develop biomarkers of Mtb infection in undernourished HHC and see if these predict TB risk. To address response to nutritional supplementation and parasite treatment, we will apply a mixed model using the dream R package [52] to account for the repeated measures analysis. We will use an FDR threshold of 0.05 to control for multiple comparisons.

#### Participant data

Participant data pertaining to demographics, socioeconomic status, food insecurity, anthropometry, and body composition will be analyzed through multivariate regression models. All models will be adjusted for independent variables and confounders to assess relative risk. Cross group comparisons will be made through ANOVA analyses.

